## Abstract

**Background:**

Endocrine therapy with ovarian function suppression combined with aromatase inhibitors or tamoxifen is essential for hormone receptor-positive breast cancer in premenopausal women, but often induces genitourinary syndrome of menopause (GSM) via hypoestrogenism. Existing research focuses on natural menopause, with limited longitudinal data on vaginal microbiome changes in breast cancer survivors, especially amid rising cases among young Chinese women.

**Objectives:**

To (1) assess temporal effects of endocrine therapy on vaginal microbiome *α*- and *β*-diversity and dominant taxa (e.g., Lactobacillus); (2) explore dose–response links between microbiome shifts and GSM severity; and (3) compare OFS + AI versus OFS + TAM impacts on vaginal microecology.

**Methods:**

This single-center prospective cohort at Women’s Hospital, Zhejiang University School of Medicine, will enroll 110 premenopausal women (18–45 years) with hormone receptor-positive breast cancer, allocated to OFS + AI or OFS + TAM based on clinical regimens. Vaginal swabs collected at baseline and 1, 3, 6, 12 months undergo 16S rRNA sequencing (V3-V4 region) with DADA2-based ASV analysis via QIIME 2 for species-level resolution. Assessments include Vaginal Health Index (VHI), GSM symptoms (VAS for dryness, dyspareunia, burning), s, and urinary symptoms (ICIQ-SF). Primary outcomes: microbiome diversity (Simpson index) and Lactobacillus abundance. Secondary: VHI, VAS, urinary scores. Analyses use repeated measures ANOVA and generalized estimating equations; sample size accounts for medium effect (*d* = 0.8) and 10% attrition. Ethically approved and registered in Chinese Clinical Trial Registry.

**Conclusion:**

As a longitudinal study on vaginal microecology in this population, this protocol integrates molecular and clinical data to reveal GSM mechanisms, informing personalized interventions for better quality of life and adherence.

**Clinical trial registration:**

http://www.chictr.org.cn/showproj.html?proj=296570, Identifier (No. ChiCTR2500115283)

## Introduction

Breast cancer continues to be the most prevalent malignancy among women worldwide, with its incidence rate persistently increasing and exhibiting a notable shift toward younger age groups in recent years. According to the most recent global cancer burden data, China reported 357,200 newly diagnosed breast cancer cases in 2022, with 20–30% of these cases occurring in women under the age of 50, and 7% diagnosed before the age of 40 (1, 2). For premenopausal patients with hormone receptor-positive breast cancer, endocrine therapy has emerged as a crucial strategy for enhancing survival outcomes (3). Substantial evidence from randomized controlled trials has demonstrated that ovarian function suppression in combination with either aromatase inhibitors or tamoxifen significantly improves disease-free survival compared to tamoxifen monotherapy (4, 5). Consequently, this combination regimen has been endorsed by authoritative guidelines, including those from the National Comprehensive Cancer Network (NCCN) and the European Society for Medical Oncology (ESMO), as the standard treatment approach for high-risk premenopausal breast cancer patients.

Nevertheless, the majority of young breast cancer survivors undergoing prolonged anti-estrogen therapy, chemotherapy-induced amenorrhea, and premature ovarian insufficiency experience varying degrees of hypoestrogenic symptoms during treatment. Among these, the symptoms associated with GSM are particularly pronounced, including vaginal dryness, burning sensations, dysuria, and dyspareunia, which tend to progressively worsen. Research indicates that approximately 70% of patients develop GSM symptoms, such as vaginal dryness and dyspareunia, following treatment with ovarian function suppression in combination with tamoxifen or aromatase inhibitors (5, 6). These symptoms significantly impair quality of life and subsequently compromise treatment adherence. Research suggests that 20–30% of breast cancer survivors cease endocrine therapy as a result of adverse effects associated with hypoestrogenism (7). In contrast to natural menopause, drug-induced “chemical menopause” is marked by a sudden onset, more severe symptoms, and typically occurs approximately 20 years earlier than physiological menopause, thereby exerting a significant psychological burden on younger women (5, 8).

The vaginal microecosystem is crucial for maintaining the health of the reproductive tract (9, 10). Previous studies have thoroughly elucidates the molecular mechanisms and therapeutic strategies related to the female vaginal microbiome (10, 11). Estrogen deficiency leads to atrophy of the vaginal epithelium and depletion of glycogen, which compromises the survival of Lactobacillus species and results in dysbiosis, increased pH, and exacerbation of GSM symptoms (12, 13). Cross-sectional studies have shown that postmenopausal women exhibit increased vaginal microbial diversity with a significant reduction in Lactobacillus, which strongly correlates with GSM symptoms (14, 15). A multicenter analysis conducted in 2024 demonstrated that non-Lactobacillus-dominant microbial states, such as the enrichment of Gram-negative bacteria, significantly increase the risk of GSM development, further confirming that vaginal dysbiosis is an independent risk factor for GSM (16). Consequently, changes in the vaginal microbiome represent a crucial aspect of the pathophysiology of GSM. The depletion of Lactobacillus species and the proliferation of anaerobic bacteria are not only indicative of the GSM vaginal microenvironment but may also directly induce symptoms via inflammatory and metabolic pathways (15–20). Profiling the vaginal microbiome shows potential as a biomarker for assessing GSM risk, which could inform predictive, preventive, and precision intervention strategies in the management of GSM.

Although the clinical characterization of GSM in perimenopausal and postmenopausal women is well-established, investigations into its relationship with alterations in the vaginal microbiome among breast cancer survivors remain limited. Prasanchit et al. (21) examined 40 postmenopausal breast cancer survivors undergoing aromatase inhibitor therapy. The study found that symptomatic patients exhibited a significantly increased vaginal abundance of Sneathia and Gardnerella, whereas asymptomatic patients showed a higher abundance of Parvimonas. These findings suggest a potential link between alterations in the vaginal microbiome and GSM symptoms. This study was constrained by several limitations, including a small sample size, a cross-sectional design that precludes causal inference, and the lack of serum estrogen validation. A study conducted in Kazakhstan in 2021 examined the vaginal microbiome of 278 breast cancer patients, comprising 174 individuals undergoing combination therapy and 104 former patients. The study identified a significant depletion of Lactobacillus, although no substantial differences in microbial composition were observed across different cancer subtypes. Patients with Luminal A/B subtypes exhibited higher proportions of anaerobic bacteria, whereas those with Her2/Neu + and triple-negative subtypes were associated with specific pathogenic bacteria, such as Staphylococcus (22). However, this study did not investigate the relationship between the microbiome and breast cancer treatment or GSM.

In summary, while recent pioneering studies have begun to explore the longitudinal changes in the vaginal microecology of breast cancer patients undergoing endocrine therapy (23, 24), key knowledge gaps persist regarding the comparative effects of OFS + AI versus OFS + TAM on vaginal microbiota dynamics and the dose–response relationships between microbiome shifts and GSM severity. Therefore, this prospective cohort study aims to further contribute to this growing body of evidence by evaluating the effect of endocrine therapy on vaginal microbiome and GSM. This prospective cohort study aims to: (1) characterize the temporal changes in vaginal microbiome *α*-diversity (Simpson index), *β*-diversity, and relative abundance of predominant taxa (particularly Lactobacillus species) over 12 months in patients receiving endocrine therapy with ovarian function suppression; (2) compare the impact of two common regimens-ovarian function suppression combined with aromatase inhibitors (OFS + AI) versus ovarian function suppression combined with tamoxifen (OFS + TAM)-on vaginal microbiome composition; and (3) explore the associations between these microbiome changes and the severity of GSM symptoms, including potential dose–response relationships, as assessed by validated clinical measures (Vaginal Health Index, visual analog scales, and urinary symptom scores).

## Methods and analysis

### Study design

This study is a single-center, prospective, longitudinal cohort investigation aimed at establishing a cohort of premenopausal breast cancer patients under the age of 45, who are hormone receptor-positive and receiving either ovarian function suppression plus aromatase inhibitors or ovarian function suppression plus tamoxifen endocrine therapy (Figure 1). The research employs a prospective design, with patient recruitment set to begin on January 1, 2026, to develop a comprehensive clinical database and biospecimen repository. This study is set to be conducted at the Women’s Hospital, Zhejiang University School of Medicine. Patient recruitment begin from January 2026 and will continue until the target sample size is achieved (anticipated 1 to 2 years). Each enrolled participant will be followed up for a full 12 months, with planned study visits and sample collections at time point of 1 month, 3 months, 6 months, and 12 months. We ensure every participant can complete the full 12-month follow-up schedule.

**Figure 1 fig1:**
[figure not shown]
Flowchart of the study.

The Women’s Hospital at Zhejiang University School of Medicine is designated as the primary coordinating center, tasked with overseeing the comprehensive study design, implementation, quality control, and data management. The research initiative will be spearheaded by a Principal Investigator (PI) who possesses specialized expertise in breast cancer research and clinical management. The PI will be responsible for the daily operations of the study, including participant recruitment, data collection, and quality assurance. Consistent with standard oncology practice in China, all patients receive comprehensive care managed by a multidisciplinary team (MDT). Following MDT consensus, our core research team consist of specialists from various clinical disciplines integral to the management of breast cancer, such as: breast surgeons with proficiency in oncologic surgery and systemic therapy, pathologists skilled in breast cancer diagnosis and molecular characterization, diagnostic radiologists with specialization in breast imaging, and gynecologists equipped to address the unique hormonal considerations in premenopausal patients, and so on.

All participants were mandated to provide written informed consent, comprehensively outlining the study’s objectives, procedures, potential risks, and benefits, thereby ensuring participants’ full comprehension of the study content and voluntary participation. For ancillary studies involving the collection of biological samples and genetic testing, distinct informed consent forms were developed to further protect participants’ rights to information and autonomous decision-making. The study protocol received approval from the Research.

Ethics Board of Women’s Hospital, Zhejiang University School of Medicine (IRB-20250423-R) and was conducted in strict adherence to the Declaration of Helsinki and pertinent national regulations. An independent safety monitoring committee was established to ensure adequate protection of subject safety and legal rights. In addition, a research quality and data quality monitoring committee, jointly established by the hospital’s ethics committee, medical affairs department, research department, and data management center, reviews our raw data every quarter to ensure the smooth progress of this study.

This study has been officially registered in the Chinese Clinical Trial Registry under the registration number ChiCTR2500115283, thereby ensuring transparency and traceability of the research process. In parallel, a comprehensive quality assurance framework has been implemented, which includes standardized operating procedures, regular training for the research team, stringent data quality control measures, periodic monitoring and auditing, and a robust documentation management system. These organizational structures and management strategies are designed to ensure the scientific rigor, regulatory compliance, and reliability of the study.

### Patient involvement

The inclusion criteria for the study are as follows: (1) Female participants aged between 18 and 45 years; (2) Histopathological confirmation of invasive breast carcinoma; (3) Positive status for hormone receptors, specifically estrogen receptor (ER) and/or progesterone receptor (PR); (4) Premenopausal status at diagnosis, characterized by baseline follicle-stimulating hormone levels below 40 IU/L and estradiol levels exceeding 20 pg./mL; (5) Scheduled to undergo ovarian function suppression in conjunction with endocrine therapy; (6) Absence of GSM-related symptoms prior to the initiation of treatment; (7) Provision of written informed consent by the participants.

Exclusion criteria included: (1) the presence of concurrent malignancies; (2) severe dysfunction of cardiac, hepatic, or renal systems; (3) pregnancy or lactation; (4) a history of vaginal infection; (5) the use of antibiotics or hormonal medications within the preceding 3 months; (6) an expected survival of less than 2 years [determined by the PREDICT tool^1^ or multidisciplinary team consensus]; (7) patients with psychiatric disorders or those who have been on active treatment with medications known to significantly alter sexual function (e.g., SSRIs, SNRIs); and (8) Patients with active high-risk HPV infections or abnormal cervical cytology requiring intervention.

This study employed a systematic recruitment strategy at Women’s Hospital, Zhejiang University School of Medicine, leveraging its role as a regional center for breast cancer care. Research coordinators reviewed pathology reports daily to identify newly diagnosed patients, conducting preliminary screenings based on age and demographics to compile a list of potential participants. Recruitment was timed post-diagnosis disclosure but pre-treatment planning to enhance receptivity, avoiding the day of diagnosis to reduce emotional burden.

The structured process included: (1) Initial clinician-led introduction during routine visits, with interested patients referred to the research team; (2) Face-to-face detailed explanations of study objectives, procedures, risks, and benefits by coordinators or nurses; (3) A minimum 24-h consideration period without pressure; (4) Signing of informed consent after addressing queries; and (5) Immediate baseline data collection and examinations. This approach aimed to minimize bias and ensure ethical enrollment of 110 participants over 6 months.

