A propensity score for receiving OFS + AI versus OFS + TAM will be estimated using a multivariable logistic regression model incorporating key baseline covariates, including age, BMI, tumor stage, prior chemotherapy exposure, and baseline ovarian function. Inverse Probability of Treatment Weighting (IPTW) will be used as the primary approach to balance baseline characteristics between the two groups. Stabilized weights will be calculated, which are truncated at the 1st and 99th percentiles to mitigate the influence of extreme weights. Standardized mean differences (SMD) will be assessed to confirm covariate balance, with an SMD < 0.1 considered acceptable.

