### Vaginal microbiome sample collection and storage

Participants were instructed to abstain from sexual intercourse, vaginal medication, and douching for 48 h prior to sampling. For patients who are menstruating at baseline, sampling was scheduled 3–7 days after the cessation of menstruation to minimize interference from the menstrual cycle. At follow-up visits, most participants will be amenorrheic due to OFS; however, if a participant reports any vaginal bleeding, sampling will be rescheduled until bleeding has ceased for at least 3 days. During the procedure, patients were placed in the lithotomy position. A sterile vaginal speculum was used to fully expose the cervix. A sterile cotton swab was rotated in the posterior vaginal fornix for 10 s to collect the specimen, since this anatomical reservoir pools cervicovaginal secretions, providing a highly representative and stable sample of the vaginal microbiome and mucosal microenvironment. The swab was immediately placed into a sterile tube containing DNA/RNA Shield™ preservative, temporarily stored at 4 °C, and transferred to a – 80 °C ultra-low temperature freezer within 4 h for long-term storage.

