### Primary outcome

This study identified vaginal microbial diversity and the relative abundance of Lactobacillus as the primary outcome measures. High-throughput sequencing of the 16S rRNA V3-V4 region was utilized, and bioinformatics analysis was conducted using the DADA2 pipeline via QIIME 2 to generate ASVs, enabling single-nucleotide resolution for quantitative assessment of alterations in vaginal microecological diversity. Species-level identification, particularly for Lactobacillus species, will be performed based on ASV taxonomic assignment. Simultaneously, the relative abundance of the Lactobacillus genus within the total bacterial community was analyzed to evaluate vaginal microecological homeostasis. Measurement time points were established at baseline, and at 1 month, 3 months, 6 months, and 12 months post-treatment, thereby creating a comprehensive longitudinal observation trajectory.

The collection of vaginal microbial samples followed a strictly standardized procedure: participants were instructed to abstain from sexual intercourse, vaginal medications, and douching for 48 h prior to sampling. Additionally, individuals who were menstruating were scheduled for sampling within a 3- to 7-day window following the cessation of menstruation to minimize interference from the menstrual cycle. During the sampling process, participants were positioned in the lithotomy position, and the cervix was fully exposed using a sterile vaginal speculum. A sterile cotton swab was rotated in the posterior vaginal fornix for a duration of 10 s, subsequently placed into a sterile tube containing DNA/RNA Shield preservative, temporarily stored at 4 °C, and then transferred to a – 80 °C ultra-low temperature freezer for long-term storage within 4 hours.

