### Secondary outcomes

Prior to inclusion (at baseline), all patients undergo a systematic evaluation of GSM symptoms using standardized questionnaires, and only patients who report no GSM symptoms are eligible for inclusion. The clinical functional indicators comprised the Vaginal Health Index (VHI), Visual Analog Scale (VAS) scores for GSM, and International Consultation on Incontinence Questionnaire (ICIQ) scores for urinary symptoms. The VHI evaluated five dimensions through gynecological examination: vaginal discharge, pH value, epithelial integrity, moisture, and elasticity, with a cumulative score ranging from 5 to 25 points. Two attending gynecologists from our core multidisciplinary research team, each with over 10 years of clinical experience specializing in gynecological oncology and reproductive endocrinology, independently assessed the scores after undergoing protocol-specific standardized training to minimize inter-observer variability. The scores were then averaged, with measurements taken at time points baseline, 3 months, 6 months, and 12 months. GSM symptoms were assessed using a 10-cm VAS to independently evaluate subjective symptoms such as vaginal dryness, dyspareunia, and burning sensation, with scores ranging from 0 to 10 (0 indicating no symptoms and 10 indicating the most severe symptoms), completed by patients at each time point from baseline to 12 months. Urinary symptoms were evaluated using the International Consultation on Incontinence Questionnaire-Short Form (ICIQ-SF), with scores ranging from 0 to 21 points, measured at baseline, 3 months, 6 months, and 12 months, to encompass the full spectrum of genitourinary syndrome manifestations. Patients independently completed symptom questionnaires under the on-site guidance of research assistants, and comprehensive documentation of medication adherence, lifestyle changes, and other relevant factors potentially influencing vaginal microecology was maintained at each follow-up visit. The results are systematically documented in the electronic Case Report Form for all participants.

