Nonetheless, the study does have some limitations. Being a single-center investigation, its results may lack generalizability; thus, multicenter studies are needed to validate the findings. Furthermore, the 12-month follow-up period may not be sufficient to fully capture the long-term dynamics of the vaginal microbiome and GSM symptomatology. Additionally, the use of 16S rRNA gene sequencing is limited to the genus level, potentially overlooking critical species-level changes. Future research should incorporate multi-omics approaches, including metagenomics and metabolomics, to yield a more comprehensive analysis. To address these limitations, this study will apply statistical adjustments and sensitivity analyses to verify the robustness of the results.

Building upon the anticipated outcomes of this study, future research directions can be delineated into four principal areas. The first area involves the execution of multicenter randomized controlled trials aimed at validating the preventive efficacy of microbiota-targeted interventions. These interventions may include supplementation with specific Lactobacillus strains, personalized probiotic therapies, or the clinical application of microecological modulators. Such trials are essential to generate high-quality evidence that can inform evidence-based medical practice.

Secondly, the integration of multi-omics analytical technologies, including metagenomics, transcriptomics, and metabolomics, is essential for a comprehensive elucidation of the molecular mechanisms underlying microbiota-host interactions. This approach aims to clarify the pathophysiological pathways through which vaginal microecological dysbiosis contributes to genitourinary syndrome of menopause (GSM) symptoms, thereby establishing a foundation for the development of novel therapeutic targets.

Third, it is imperative to expand to international multicenter cohort studies that incorporate diverse racial and geographic populations. This approach will enhance the generalizability of research findings and inform the development of international guidelines. Simultaneously, it is crucial to explore the influence of genetic polymorphisms on vaginal microecology to advance precision medicine applications in the management of genitourinary syndrome of menopause (GSM).

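### Oral and vaginal probiotic (Lactobacillus) products are named neither in the 3-month washout nor in the listed baseline data, although Lactobacillus abundance is a primary outcome

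*Protocol article*

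**What the plan says.** Patient involvement sets out seven inclusion and eight exclusion criteria. The one with a washout period is exclusion 5: "the use of antibiotics or hormonal medications within the preceding 3 months". No criterion mentions probiotics or Lactobacillus products.

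The Primary outcome section names "vaginal microbial diversity and the relative abundance of Lactobacillus as the primary outcome measures", and states that "the relative abundance of the Lactobacillus genus within the total bacterial community was analyzed to evaluate vaginal microecological homeostasis". The first measurement is at baseline.

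Two other provisions come close to the point:
- Sample collection: "Participants were instructed to abstain from sexual intercourse, vaginal medication, and douching for 48 h prior to sampling".
- Secondary outcomes: documentation of adherence, lifestyle and "other relevant factors potentially influencing vaginal microecology was maintained at each follow-up visit".

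The propensity score for the weighting uses key baseline covariates, "including age, BMI, tumor stage, prior chemotherapy exposure, and baseline ovarian function". The baseline data listed just before it cover demographic, tumour, treatment and laboratory items. The Discussion mentions probiotics only as a subject for later work. There it counts "supplementation with specific Lactobacillus strains, personalized probiotic therapies" among interventions directed at the microbiota.

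**The concern.** The protocol already accepts that a recent exposure can disturb the baseline flora: it sets a 3-month washout for two drug classes. The list leaves out the product class that supplies the genus being measured. Because the outcome is the share of the whole genus, Lactobacillus sequences count towards it whatever their source.

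Baseline is the reference for the first aim, change over 12 months. If a user stops her product after entry, any resulting fall in Lactobacillus points the same way as the effect that the Discussion hypothesises for endocrine therapy. The groups are not randomised, so unequal use could also add to or mask the difference between OFS + AI and OFS + TAM. Weighting does not correct for a covariate that is not in the propensity model.

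**Working it through.** The plan gives no figure on this point, so there is none to reproduce. The check is a reading of each place where the exposure could be controlled, followed by an illustration.

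**Step 1. Where could probiotic use be caught?**

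| Place in the Protocol article | What it covers | Does it protect baseline? |
|---|---|---|
| Exclusion 5 | Antibiotics and hormonal medications, 3 months | Not for probiotics |
| Exclusion 4 (past vaginal infection) and inclusion 6 (no GSM symptoms) | Women with two plausible reasons for using vaginal products | Indirectly, by lowering use |
| 48-hour rule before sampling | Vaginal medication | Briefly, if a vaginal probiotic counts as medication; oral products are not covered |
| Baseline data under Cohort classification | No such product named | Not as listed |
| Table 1, baseline column | Medical history, in general terms | Possibly, but capture of over-the-counter products is not assured |
| Record of other factors (Secondary outcomes) | General, at follow-up visits | No, baseline is not included |
| Propensity covariates (Cohort classification; Statistical analysis) and regression confounders (Statistical analysis) | Probiotic use not named | Not as listed |

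A current user meets every stated criterion, and no provision is specific to her at baseline.

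**Step 2. How large could the effect be?** The documents give neither the proportion of users nor the shift per user. The values here are assumptions, used only to show the scale.

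Shift in the baseline mean = proportion of users × gain in relative abundance per user.
- Low: 0.05 × 10 points = 0.5 points.
- High: 0.20 × 30 points = 6 points.

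If every user stopped after entry and lost the whole gain, a spurious fall of the same size would appear in the cohort mean.

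Spurious baseline difference between groups = (difference in proportion of users) × gain per user.
- Equal use in both groups: 0 × gain = 0 points.
- 10% against 5%, gain 10 points: 0.05 × 10 = 0.5 points.
- 20% against 10%, gain 30 points: 0.10 × 30 = 3 points.
- All use in one of two equal groups, top of both ranges: 2 × 6 = 12 points. This is an extreme case, and nothing in the documents suggests it.

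The share is also bounded above, so a woman whose flora is already dominated by Lactobacillus can gain little.

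**Step 3. What would an exclusion cost in numbers?** The Sample size section expects 200 to 300 eligible women and a recruitment rate of 40% to 50%: 0.40 × 200 = 80 to 0.50 × 300 = 150, against a target of 110. Losing 5% leaves 76 to 142.5. Losing 20% leaves 64 to 120.

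**The case against.** The strongest reply is that much of this may already be dealt with out of sight. The article words its lists openly, so the items given are examples. Table 1 collects medical history at baseline, and a concomitant-product item is the kind of detail an article leaves to the full protocol or the eCRF. A reader might infer from the lists that users can be neither excluded nor adjusted for. The documents do not support that: they show only that no stated provision names these products. This part of the reply stands.

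It also stands that exclusion 4 and inclusion 6 probably lower use, particularly of vaginal products, and that the harm is not demonstrated. The Discussion treats probiotics as interventions whose preventive efficacy still needs randomised trials. That shows an intended action on the flora, not a measured shift. No mechanism is given by which users would gather in one regimen.

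The reply does not remove the point. Eligibility is protocol content, and the article itself chose a washout and named its classes. Exposure that is not recorded at baseline is hard to reconstruct later, and neither the 48-hour rule nor a record kept at follow-up protects the reference measurement.

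**Conclusion.** The point holds as a cheap improvement of low severity. As written, users of oral or vaginal Lactobacillus products can enter, and neither exclusion 5 nor the listed baseline data name the exposure. In those women, the baseline value of both primary outcomes may partly reflect the product.

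A reader might go further and conclude that the primary outcome is contaminated, or that the regimen comparison is biased by several points. The documents do not support either conclusion. The effect concerns users only, their number and the gain per user are unknown, and with equal use the spurious baseline difference between groups is zero. The range of 0.5 to 6 points for the cohort mean rests entirely on the assumed 5% to 20% use and 10 to 30 point gain.

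**What to change.** Preferred: extend the 3-month rule in exclusion 5 to oral and vaginal probiotic (Lactobacillus) products, and name them in the baseline record.

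Minimum: do not exclude users, but record use at baseline and include it as a covariate in the propensity score and the outcome models. This is weaker in two ways. It can balance the groups, but it does not undo a fall that follows when a user stops. And with few users its coefficient would be poorly estimated: at the assumed 5%, 0.05 × 55 = 2.75, or about 3 women per group.

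In either case, name probiotic use in the existing follow-up record and use it only in a sensitivity analysis. It should not enter the primary models as a time-varying covariate. Use after baseline may be a response to symptoms that the regimen caused, and adjusting for it could bias the comparison of regimens.

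Cost: one phrase in the criteria, one eCRF item, and some women deferred or lost at screening. The baseline swab must precede endocrine therapy, so deferral will not always be possible. If use is rare the loss is a few women. If it approached 20%, the expected yield of 64 to 120 would put the target of 110 at more risk, and the minimum option would be the better choice.
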